### Model validation

The predictive performance of each model will be assessed in terms of discrimination, that is the ability to distinguish between those who do or do not have a particular diagnosis, and calibration meaning agreement between predicted and observed probabilities. Discriminative ability will be assessed using the c-index and its 95% CIs. For a logistic model, this is equivalent to the area under the Receiver Operator Characteristic (ROC) curve. Calibration will be evaluated in two ways. Calibration plots of average observed probability against predicted probability will be used to visually assess calibration. Within each quintile or decile of predicted probability (depending on the distribution of data), the average predicted probability will be compared with the corresponding observed proportions. We will also quantify calibration by estimating the calibration slope of the prognostic index (linear predictor) using logistic regression with the linear predictor as the covariate.

The apparent c-index and calibration slope will be estimated for each model. Bootstrapping will be used for internal validation to assess model overfitting and optimism. For each model, we will obtain 100 bootstrap samples from each imputed data set and repeat the variable selection process. The optimism is the difference between the c-index from the bootstrap sample and that from the original imputed data set. The average optimism will be determined across bootstrap samples and imputed data sets, and the optimism-adjusted c-index will be calculated by subtracting the average optimism from the apparent c-index of the original model. Similarly, we will obtain the optimism-adjusted calibration slope. The optimism-adjusted calibration slope will be used as the uniform shrinkage factor to correct a model.

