We will externally validate the models and calculate performance statistics (c-index and calibration slope) using the validation cohort. The value for the calibration slope should ideally be one signifying perfect agreement between the predicted probabilities and the observed probabilities. A calibration slope <1 indicates that a model overpredicts while a calibration slope >1 indicates underprediction. From the qualitative research, we will ascertain distributions of probability (risk) thresholds for clinical usefulness of the prediction in guiding treatment of each condition. The sensitivity and specificity (and their corresponding 95% CIs) will be calculated for these risk thresholds and plotted on an ROC plot for each model.

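### External calibration is quantified by the slope alone, and the slope is misread as a measure of over- or underprediction; a calibration-in-the-large estimate is needed beside it

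*Protocol article*

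**What the plan says.** All the relevant text is in the protocol article, Statistical analysis, Model validation.

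- Calibration is to be assessed in two ways. One is graphical and grouped: "Calibration plots of average observed probability against predicted probability will be used to visually assess calibration", and within quintiles or deciles of predicted risk "the average predicted probability will be compared with the corresponding observed proportions". The other is numerical: a calibration slope, estimated "using logistic regression with the linear predictor as the covariate".
- After bootstrapping, "The optimism-adjusted calibration slope will be used as the uniform shrinkage factor to correct a model". The text does not say which terms are multiplied or what happens to the intercept.
- For the validation cohort: "We will externally validate the models and calculate performance statistics (c-index and calibration slope) using the validation cohort". No calibration intercept or observed/expected ratio is named.
- The slope is then interpreted. A value of one is taken to mean that predicted and observed probabilities agree completely, and "A calibration slope <1 indicates that a model overpredicts while a calibration slope >1 indicates underprediction".
- On thresholds that come from the qualitative work: "The sensitivity and specificity (and their corresponding 95% CIs) will be calculated for these risk thresholds". Sensitivity and specificity are the primary outcome (Primary outcome section).

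**The concern.** The models deliver absolute probabilities, and the primary outcome is taken at absolute risk thresholds. What matters at a threshold is whether a predicted 20% is an actual 20%. That has two parts: whether predictions are right on average, and whether their spread is right. The slope measures only the spread. The article gives it both jobs.

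If every predicted risk in the validation cohort were too high by the same amount on the logit scale, the c-index would not change and the slope could still be exactly one. Under the article's own reading, such a model would be reported as in full agreement. A slope of 0.8 would be reported as overprediction, although it says nothing about the average.

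There are two plausible sources of a shift. Prevalence may differ between the first 350 and the next 325 data sets; the article itself lists uncertain prevalence as a limitation. And uniform shrinkage moves the average risk unless the intercept is re-estimated afterwards.

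**Working it through.** **Inputs.** From the Sample size section: prevalences of 57% (detrusor overactivity, DO), 31% (bladder outlet obstruction, BOO) and 16% (DU), and a validation cohort of 325. Assumed, because the article gives neither: shrinkage factor *s* of 0.7 to 0.9, and a normally distributed linear predictor (LP) with SD 1.

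**1. The article's own count.** 325 × 0.16 = 52 DU cases and 273 non-cases, as stated.

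**2. The slope does not respond to a shift.** The slope *b* comes from logit P(Y=1) = *a* + *b*·LP. Replace LP by LP + *d*, so that every prediction moves by *d* on the logit scale. The refitted model is (*a* − *b·d*) + *b*·(LP + *d*): the intercept absorbs the shift and *b* is unchanged. Ranks, and so the c-index, are unchanged too.

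A simulation agrees (12 uncentred predictors, 350 development and 20,000 validation subjects, 40 runs per condition, assumed coefficients). For DU, three ways of handling the intercept after shrinkage gave mean predicted risks of 14.4% (left as it was), 26.8% (shrunk too) and 16.1% (re-estimated). The validation slope was 1.12 in all three.

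**3. What a slope below 1 means.** Take *b* = 0.8, with predicted and true risk equal at 16% (logit −1.658).

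| Position on the LP | Predicted risk | True risk |
|---|---|---|
| One unit above | expit(−0.658) = 34.1% | expit(−1.658 + 0.8) = 29.8% |
| One unit below | expit(−2.658) = 6.5% | expit(−1.658 − 0.8) = 7.9% |

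The same model overpredicts at high risk and underpredicts at low risk.

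**4. Effect of a shift at a threshold.** Suppose all predicted odds are inflated by (0.20/0.80)/(0.16/0.84) = 1.3125, or 0.272 on the logit scale. A nominal 20% threshold then selects men whose correct risk exceeds expit(−1.386 − 0.272) = 16%. The ROC curve is the same, but the operating point differs from the one labelled.

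**5. How large a shift could shrinkage cause?** Choose *a* so that the mean of expit(*a* + Z) equals the prevalence, with Z standard normal; for DU, *a* = −1.961. Then compute the mean predicted risk after shrinkage without re-estimating the intercept.

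| Condition | *s* | Centred coefficients shrunk, expit(*a* + *s*Z) | Whole LP shrunk, expit(*s*(*a* + Z)) |
|---|---|---|---|
| DU, 16% | 0.7 | 14.2% | 22.3% |
| DU, 16% | 0.8 | 14.8% | 19.9% |
| DU, 16% | 0.9 | 15.4% | 17.8% |
| BOO, 31% | 0.8 | 30.0% | 33.7% |
| DO, 57% | 0.8 | 57.4% | 55.9% |

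With uncentred predictors the range is wider. At *s* = 0.8 and an assumed c-index of 0.75, DU runs from 9.0% to 23.3% for mean predictor contributions from +3 to −3 logits, which are also assumed. With the intercept re-estimated, the mean returns to 57.0%, 31.0% and 16.0%.

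**6. How well can the planned checks see it?** Take the standard error of an observed proportion, √(p(1−p)/n), at p = 0.16 as a round figure for every group.

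| Unit | n | SE (points) | A 4-point shift in SEs |
|---|---|---|---|
| Decile | 32.5 | 6.4 | 0.6 |
| Quintile | 65 | 4.5 | 0.9 |
| Whole cohort | 325 | 2.0 | 2.0 |

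The information on average calibration lies in the whole-cohort comparison, which the plan does not list.

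**The case against.** Three objections deserve weight.

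**The shrinkage sentence is silent, not wrong.** A reader might infer that the intercept is left alone or multiplied, so that the corrected models must carry a wrong average risk. The article says neither. It names the factor and nothing more, and a condensed article may leave the intercept step to the full protocol or analysis plan. The two possible readings even err in opposite directions for DU (below and above 16%), so no wrong result is fixed by the text. This objection stands, and the intercept step is only a matter for clarification.

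**Calibration plots and a grouped comparison are planned.** They compare mean predicted with observed risk and would display a shift, so it would be wrong to say that the plan cannot reveal one. This also stands. What remains is that they are visual or split into small groups, give no single estimate with an interval, and are weakest for DU.

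**A shift only slides the operating point along an unchanged ROC curve.** That is true, and results are to be plotted on an ROC plot. But sensitivity and specificity are reported at named risk thresholds, and those values do move.

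None of the three touches the sentence that interprets the slope. That is a positive statement, and further detail elsewhere would have to correct it, not merely add to it.

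**Conclusion.** The point holds in two parts. The stated interpretation of the slope is wrong: a slope of one does not establish agreement, and a slope below or above one is not over- or underprediction on average. And the numerical statistics named for external validation, c-index and slope, leave average calibration without an estimate, although the primary outcome depends on absolute risk.

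No error in average risk is shown. If the intercept were not re-estimated, the DU mean at *s* = 0.8 and LP SD 1 would be off by about 1 point (centred coefficients) or 4 points (whole LP). These sizes rest on an assumed shrinkage factor, discrimination and centring. The algebra in steps 2 and 3 does not depend on those assumptions.

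**What to change.** 1. Add calibration-in-the-large to the validation statistics for each of the three models: the calibration intercept with the slope fixed at 1, or the observed/expected ratio, with a 95% CI. Report it beside the slope and keep the plots.
2. Correct the interpretation: a slope below 1 indicates predictions that are too extreme (too high at high risk, too low at low risk), and above 1 predictions that are not spread enough. Over- or underprediction on average is read from calibration-in-the-large. A slope of one alone does not establish agreement.
3. As a clarification, state that the coefficients are multiplied by the shrinkage factor and the intercept is then re-estimated in the development data with the shrunken linear predictor as offset. If the full protocol or analysis plan already says so, a cross-reference is enough.

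The cost is a few sentences, one small extra fit per model in the validation data and, if not already planned, one intercept fit per model in the development data. No new data are needed and the sample size is unaffected.

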**Trial registration number:**

ISRCTN10327305.

Strengths and limitations of this studyProspective, multicentre study in an appropriate population in primary care.The index tests are tests that can be done routinely in primary care or at home by patients.The diagnostic models developed will be validated in a separate cohort of men from the same population.The assumed prevalence of the three target conditions may be different in practice.Some test results may be missing or difficult to obtain.

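### The plan misreads the calibration slope: it measures how spread out the predictions are, not over- or underprediction, and a value of 1 alone does not show perfect agreement

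*Protocol article*

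**What the plan says.** The Model validation section of the protocol article obtains the slope by "estimating the calibration slope of the prognostic index (linear predictor) using logistic regression with the linear predictor as the covariate". For the development models, "The optimism-adjusted calibration slope will be used as the uniform shrinkage factor to correct a model".

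For external validation: "We will externally validate the models and calculate performance statistics (c-index and calibration slope) using the validation cohort". Two sentences then say how the slope is to be read: "The value for the calibration slope should ideally be one signifying perfect agreement between the predicted probabilities and the observed probabilities", and "A calibration slope <1 indicates that a model overpredicts while a calibration slope >1 indicates underprediction".

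The same section plans two direct looks at the level of the predictions. First, "Calibration plots of average observed probability against predicted probability will be used to visually assess calibration". Second, within quintiles or deciles of predicted risk, "the average predicted probability will be compared with the corresponding observed proportions".

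**The concern.** The two interpretive sentences do not fit the quantity being estimated. The slope describes the spread of the predicted log-odds relative to the truth. Average over- or underprediction is a matter of level, which is carried by the intercept with the linear predictor as offset, or by the ratio of observed to expected events.

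The sentences also sit badly with the article's own use of the slope as a shrinkage factor. Multiplying a linear predictor by a number below 1 pulls extreme predictions inward. That is the right remedy if a slope below 1 means too much spread from overfitting. It is not a remedy for predictions that are too high on average.

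The slope is the only summary calibration statistic named for external validation. If the results are written up by the stated rule, an overfitted model will be described as one that overpredicts, and a uniformly shifted model with slope 1 can be described as in perfect agreement. The tool is meant to deliver probabilities that are compared with risk thresholds, so both descriptions would mislead users and anyone recalibrating it.

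**Working it through.** The article gives no computed figure to reproduce here; what is tested is its interpretation rule.

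**Inputs.** Prevalences of 57% (DO), 31% (BOO) and 16% (DU) and a validation cohort of 325, from Sample size. The calibration model, from Model validation, is logit P(Y=1) = a + b × LP, where LP is the model's linear predictor and b is the slope. The article gives no spread for LP, so a standard deviation (SD) is assumed and varied.

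**Step 1: is slope 1 the same as agreement?** Suppose the model's LP equals the true log-odds plus a constant s. Then the true log-odds equal −s + 1 × LP, so b = 1 and a = −s for every s. No assumption about spread is needed. Large simulated samples (200,000 men, SD of the true log-odds 1.2, s = +0.5) confirm it:

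| Condition | Mean predicted | Observed | Slope | Intercept with LP as offset |
|---|---|---|---|---|
| DO | 0.66 | 0.57 | 1.00 | −0.50 |
| BOO | 0.40 | 0.31 | 0.99 | −0.51 |
| DU | 0.22 | 0.16 | 1.00 | −0.49 |

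The offset intercept recovers the shift; the slope does not register it.

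**Step 2: does a slope below 1 mean overprediction?** The model overpredicts where LP > a + b × LP. For b < 1 this is LP > a/(1 − b), so it overpredicts above that point and underpredicts below it. For b > 1 the pattern reverses.

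Example for DU: b = 0.7, model LP normal with SD 1.2, and both means fixed at 16%. Solving for the means gives an LP mean of −2.077 and a = −0.425. The crossing point is −0.425/0.3 = −1.415, a predicted risk of 19.5%. The share of men below it is Φ((−1.415 + 2.077)/1.2) = Φ(0.552) = 71%. So a model that the rule labels as overpredicting gives too low a risk to about 71% of men.

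| Assumed SD of model LP | Lowest decile, predicted vs true | Top decile, predicted vs true |
|---|---|---|
| 0.8 | 3.8% vs 6.2% | 39.0% vs 31.7% |
| 1.2 | 1.7% vs 3.5% | 50.4% vs 40.2% |
| 1.6 | 0.7% vs 2.0% | 60% vs 48.3% |

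The direction is the same at every SD; only the size changes.

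**Step 3: can the rule point the wrong way on average?** Yes. For BOO (SD of the true log-odds 1.2), a slope of 0.80 can go with mean predicted 0.21 against observed 0.31. A slope of 1.26 can go with 0.45 against 0.31. The rule would name the opposite direction in each case.

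**Step 4: would the other planned checks show a shift?** In 400 simulated validation cohorts of 325 per scenario, with s = +0.5 or +1, the slope's 95% CI contained 1 in 94% to 97%. Predicted exceeded observed in at least four of five quintiles in 94% to 100%. The grouped comparison would therefore usually show what the slope cannot.

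**The case against.** The strongest reply is that little harm follows, and much of it stands.

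- **The plan can see a shift.** A reader might infer that a model systematically too high or too low would pass unnoticed. The plots and the quintile or decile comparison look at level directly, and Step 4 shows that they would usually reveal a large shift.
- **There is no pass mark.** A reader might infer that slope 1 is an acceptance criterion. The article calls it ideal and attaches no decision to it.
- **The primary outcome is untouched.** Sensitivity and specificity are counted against urodynamics at the risk thresholds, whatever is said about the slope.
- **The prevalence limitation is a different matter.** The strengths and limitations list says "The assumed prevalence of the three target conditions may be different in practice". It is tempting to read this as a forecast of an intercept error. The assumed prevalences are sample-size inputs, whereas the model intercept is estimated from the development data. The validation men are the next 325 data sets from the same population. Nothing in the article suggests that prevalence will change between the two cohorts.
- **Silence on an intercept statistic is not a fault.** The analysis plan is not shown and may specify one.

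What the reply does not answer is that the two sentences are stated, not omitted, and are incorrect for the regression the article itself describes.

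**Conclusion.** The point holds as an error of interpretation and reporting. A slope below 1 indicates predictions that are too extreme and a slope above 1 predictions that are too compressed. Neither identifies average over- or underprediction, and a slope of 1 needs a correct level beside it before agreement can be claimed. The invariance of the slope to a shift is exact. The decile figures are illustrations that rest on a normal linear predictor with an assumed SD.

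The consequence is a wrong conclusion about the direction or presence of miscalibration, drawn from the one summary calibration statistic named for external validation. Design, sample size, model fitting and the sensitivity and specificity estimates are unaffected. It should be corrected before the validation results are written up, but it does not threaten the study.

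**What to change.** Replace the two interpretive sentences with wording such as: a slope below 1 indicates predictions that are too extreme, as with overfitting; a slope above 1 indicates predictions that are not extreme enough; a slope of 1 indicates good calibration only when the average level is also correct.

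Beside the slope and the plot, report for each of the three models calibration-in-the-large (the intercept with the linear predictor as offset) or the observed/expected ratio, with its 95% CI. Read level and slope together.

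As a suggestion only, state whether the intercept is re-estimated after the uniform shrinkage, since shrinking the whole linear predictor can itself move the average prediction.

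The cost is a wording change and one extra logistic fit per model, with no new data.

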### Missing data

Patterns of missing data will be investigated to infer the ease with which each parameter can be obtained in practice. In the event of missing data, multiple imputation by chained equations^8^ will be used to impute missing values to avoid bias and make best use of the data.

## Secondary substudies

### Study management

The study is sponsored by Cardiff University, coordinated by CTR and co-led by The Newcastle upon Tyne Hospitals NHS Foundation Trust. The other partner organisations will be Birmingham University, University of Bristol and North of England Commissioning Support.

#### Study Management Group

The Study Management Group (SMG) will meet monthly throughout the course of the study and will include the chief investigators, co-applicants, collaborators, study manager, data manager and administrator. Two patient representatives will also attend and contribute to the conception, design and management of the study, as well as patient-facing materials. SMG members will be required to sign up to the remit and conditions as set out in the SMG Charter.

#### Study Steering Committee

An independent Study Steering Committee (SSC) consisting of an independent chairperson, two independent members and two patient representatives will provide oversight of the PriMUS study. Instead of a separate Independent Data Monitoring Committee, the SSC will also provide oversight of all matters related to patient safety and data quality. Members will be required to sign up to the remit and conditions as set out in the SSC charters and will meet annually.

## Ethics and dissemination

### Research approvals

The Wales REC 6 has approved the study (17/WA/0155) on 20 June 2017 and subsequent R&D approval for Wales on 21 August 2017 and HRA approval on 23 August 2017.

All study participants will give informed consent before taking part (see earlier).

The following substantial amendments were made to the trial and were communicated to all trial sites:

Substantial Amendment 1 (3 October 2017); Substantial Amendment 2 (10 January 2018); Substantial Amendment 3 (20 April 2018); Substantial Amendment 4 (26 February 2019); Substantial Amendment 5 (6 June 2019); Substantial Amendment 6 (6 September 2019).

### Dissemination plan

Following completion of the study, a final report will be prepared for the NIHR Journal series. A paper describing the primary results will be submitted to a high impact, international, peer-reviewed journal. Qualitative studies and substudies will also be submitted for publication. We will present our findings at national and international scientific meetings.

With the assistance of our collaborators and lay representatives, we will disseminate the study findings to a wide NHS and general audience and promote uptake of outputs into clinical care. This will include presentations at meetings and written executive summaries for key stakeholder groups such as Primary Care Trusts, Secondary Care Trusts, Health Boards, Royal Colleges, Medical Schools and relevant patient groups.

All publications and presentations related to the study will be authorised by the SMG in accordance with the study’s publication policy.

10.1136/bmjopen-2020-037634.supp1Supplementary data
